### Aim 2: Adapt and Iteratively Refine Tele-BE in an Open Field Trial

We will recruit 5-10 clinician-patient dyads who are already providing or receiving telehealth therapy services to engage with Tele-BE in an open field trial. The final sample size will be determined based on when saturation is reached (see below). The primary aim of this trial is to identify software bugs and evaluate usability and acceptability issues that emerge over extended use of Tele-BE, while refining our BE strategies. Secondary goals are preliminarily assessing the extent to which Tele-BE engages target implementation mechanisms and supports clinicians in delivering CBT structural components to guide further refinements. Clinicians and patients will be recruited in pairs, with participating clinicians using Tele-BE with a consenting patient of their choice for up to 4 consecutive therapy sessions or over 5 weeks of treatment, whichever occurs first. After obtaining consent, each clinician-client dyad will receive a personalized, secure link to use during their regularly scheduled telehealth sessions for up to 5 weeks. Only the clinician will require instructions on using Tele-BE. Client participants will not view the Tele-BE interface, so their telehealth sessions will appear similar to standard care.

We will use rapid-cycle methods to test and refine both the platform and the BE features developed in aim 1, with the goal of optimizing messages and visual displays. Adjustments will be made after each dyad completes aim 2 activities, continuing until feedback saturation is reached and a version suitable for formal testing in aims 3 and 4 is achieved. To streamline this process, we will use “fake back ends” to test BE strategies whenever possible, avoiding time-consuming web programming for features that may require revision. For example, study staff may message clinicians directly to simulate portal-generated messages based on feedback. The exact content of messages may evolve over time in response to participant input. Using a fake back end allows small changes across enrolled dyads to be tested more efficiently.

As noted, the Tele-BE platform is designed to be agnostic to specific CBT interventions and only nudges the use of interventions within the standard CBT session structure. A key focus of this design phase is ensuring that clinicians understand how to “override” any recommendation to use a particular structural component, maintaining full autonomy over clinical decisions. Aside from supporting Tele-BE use during already scheduled CBT sessions, research staff will provide no guidance on session conduct. Recruiting from the BCI-trained pool of therapists ensures that the CBT structure aligns with routine care. The only restriction is that clinicians will not be asked to use Tele-BE during first patient encounters or termination sessions, as these sessions may not follow the standard structure that Tele-BE is designed to support.

After each dyad’s trial period, staff will interview clinicians and patients separately about their experiences. Clinician interviews will assess system usability using the same structured interview employed in aim 1, covering learnability, acceptability, usefulness, satisfaction with aesthetics, efficiency, and workflow integration. Semistructured questions will also explore clinicians’ perceptions of how Tele-BE influenced their use of CBT structural elements, whether it produced any desirable or undesirable effects on the session or therapeutic relationship, and whether they felt comfortable overriding platform recommendations. The final portion of the interview will solicit suggestions for improving Tele-BE. Brief patient interviews will focus on the patient experience, assessing whether Tele-BE is perceived to have any desirable or undesirable effects on the therapeutic relationship or patient-centered care processes (see Multimedia Appendix 3). Clinicians will receive US $75 and patients US $25 for participating in these activities. We will use rapid qualitative analysis procedures to synthesize feedback and identify changes needed for the next testing cycle. All feedback will be reviewed with the full research team to resolve any conflicting information.

### Aims 3 and 4: Evaluate the Preliminary Effectiveness of Tele-BE in Engaging Target Mechanisms and Enhancing Clinician Fidelity to CBT

#### Overview

Although aims 3 and 4 are scientifically distinct, study procedures will occur concurrently and are described together. We will randomize 30 clinicians who already provide individual CBT via telehealth for at least 2 clients to either Tele-BE or telehealth as usual (Tele-AU), with 15 clinicians per condition. Allocation will be balanced within organizations to ensure equal representation across conditions within each agency. Each participating clinician will deliver treatment to 2 patients over 12 weeks, the standard length for many CBT protocols, and clinician fidelity to CBT structural components will be tracked in each condition. While the primary goal is to evaluate the feasibility of our design and measurement approach for a fully powered trial, we will also measure patient symptoms, therapeutic alliance, and patient-centered care to explore preliminary clinical effectiveness outcomes and assess any potential concerns with Tele-BE (eg, clinician distraction or impact on therapeutic alliance) using mixed methods.

##### Participants and Procedures

We will identify at least 4 local agencies that use telehealth and have participated in system-sponsored BCI CBT training [55] as recruitment sites. A cascaded recruitment strategy, previously successful in other studies, will be employed to recruit 30 CBT-trained clinicians who treat study-eligible patients (ie, age 14 or older, consistent with the local age of consent for mental health services; already deemed appropriate for CBT; and already using telehealth as their preferred therapy modality). In this approach, clinicians will then help select 2 patients with whom they plan to use CBT and will approach those patients about participating in the study. If a clinician has more than 2 patients with whom they plan to use CBT, 2 patients will be randomly selected from the larger pool for study participation. After obtaining informed consent, clinicians will be randomized to either the Tele-BE or Tele-AU condition. Study procedures will be identical across conditions, with the only difference being that clinicians in the Tele-BE condition will use the new telehealth tool, while those in the Tele-AU condition will use the telehealth methods established by their organization. All sessions will be video-recorded using encrypted, HIPAA-compliant technology via the clinicians’ assigned telehealth platform. Clinicians and patients will complete questionnaires at 4 time points—baseline/week 1, week 5, week 9, and week 12—and participate in a qualitative interview posttrial (Table 2).

Clinicians will receive US $150 for completing study measures (US $50 for week 1 and posttrial, US $25 for weeks 5 and 9). Patients will receive US $5 per session for providing brief self-report data and allowing their sessions to be recorded, for a maximum of US $60; those completing qualitative interviews will receive an additional US $25. Clinicians and patients in both conditions will follow the same study activity schedule and complete the same assessment battery, except that participants in the Tele-BE condition will also respond to condition-specific qualitative interview questions. Compensation rates are consistent with our prior work.

**Table 2 table2:** Trial assessment schedule for aims 3 and 4.

Outcomes		Measures	Tele-BE^a^																										Post
				1		2		3		4		5		6		7		8		9		10		11		12			
**Aim 3 primary outcomes**																													
	Structural component fidelity	CTRS^b^ [56] and web analytics	✓		✓		✓		✓		✓		✓		✓		✓		✓		✓		✓		✓		N/A^c^		
**Aim 3 secondary outcomes**																													
	Clinician intentions	Established stems [57]	✓		N/A		N/A		N/A		✓		N/A		N/A		N/A		✓		N/A		N/A		N/A		✓		
	Clinician attitudes	Established stems [57]	✓		N/A		N/A		N/A		✓		N/A		N/A		N/A		✓		N/A		N/A		N/A		✓		
	Clinician norms	Established stems [57]	✓		N/A		N/A		N/A		✓		N/A		N/A		N/A		✓		N/A		N/A		N/A		✓		
	Clinician self-efficacy	Established stems [57]	✓		N/A		N/A		N/A		✓		N/A		N/A		N/A		✓		N/A		N/A		N/A		✓		
**Aim 4 primary outcomes**																													
	Acceptability	AIM^d^ [58] and Interview	✓		N/A		N/A		N/A		✓		N/A		N/A		N/A		✓		N/A		N/A		N/A		✓		
	Feasibility	FIM^e^ [58] and web analytics	✓		N/A		N/A		N/A		✓		N/A		N/A		N/A		✓		N/A		N/A		N/A		✓		
	Usability	SUS^f^	✓		N/A		N/A		N/A		✓		N/A		N/A		N/A		✓		N/A		N/A		N/A		✓		
**Aim 4 secondary outcomes**																													
	Patient symptoms and functioning	PHQ-8^g^, GAD-7^h^, WHODAS^i^ 2.0, and DSM^j^ level 1	✓		N/A		N/A		N/A		✓		N/A		N/A		N/A		✓		N/A		N/A		✓		N/A		
	Therapeutic alliance	WAI-SF^k^ (therapist), WAI-SF (client) [59]	✓		N/A		N/A		N/A		✓		N/A		N/A		N/A		✓		N/A		N/A		✓		N/A		
**Additional constructs of interest**																													
	Contextual factors	Qualitative interview	N/A		N/A		N/A		N/A		N/A		N/A		N/A		N/A		N/A		N/A		N/A		N/A		✓		
	Clinician and patient demographics	Demographics survey	N/A		N/A		N/A		N/A		N/A		N/A		N/A		N/A		N/A		N/A		N/A		N/A		N/A		
	Supervision practices	Adapted SerTIFY^l^-Supervision Form	✓		N/A		N/A		N/A		N/A		N/A		N/A		N/A		N/A		N/A		N/A		N/A		✓		
	Clinician social desirability	Edward’s Social Desirability scale	✓		N/A		N/A		N/A		N/A		N/A		N/A		N/A		N/A		N/A		N/A		N/A		N/A		
	Tele-BE costs	Qualitative interview and web analytics	N/A		N/A		N/A		N/A		N/A		N/A		N/A		N/A		N/A		N/A		N/A		N/A		✓		

^a^Tele-AU: telehealth as usual.

^b^CTRS: Cognitive Therapy Rating Scale.

^c^N/A: not applicable.

^d^AIM: Acceptability of Intervention Measure.

^e^FIM: Feasibility of Intervention Measure.

^f^SUS: System Usability Scale.

^g^PHQ-8: 8-item Patient Health Questionnaire.

^h^GAD-7: 7-item Generalized Anxiety Disorder Scale.

^i^WHODAS: WHO Disability Assessment Schedule 2.0.

^j^DSM: Diagnostic and Statistical Manual of Mental Disorders.

^k^WAI-SF: Working Alliance Inventory—Short Form.

^l^SerTIFY: Self-reported therapist intervention fidelity for youth supervisor.

#### Quantitative Measures: Aim 3 Primary Outcomes

The primary outcome for aim 3 is clinician fidelity to structural components of CBT. We will code all recorded therapy sessions (up to 720 sessions: 60 patients × 12 sessions) for the presence of 6 structural components: (1) discussion or review of patient symptoms, (2) homework review, (3) agenda setting, (4) skill instruction or review, (5) skill practice, and (6) out-of-session practice (homework). Coding will use items from the CTRS, a gold-standard CBT fidelity measure with 11 observer-rated items, including those indexing the specific structural components of interest (homework review and planning, agenda setting, skill instruction, and skill practice) [60]. Each CTRS item is scored on a 7-point Likert scale ranging from 0 (poor) to 6 (excellent), allowing fidelity to be defined in 2 ways: (1) the presence or absence of each component, and (2) whether each component meets a competency threshold (ie, a score of 4 or higher). Our primary focus will be on the presence/absence of each component, calculated as the sum of the binary outcomes. Presence above the competency threshold will serve as a secondary outcome. The CTRS demonstrates strong internal consistency and interrater reliability [60], as well as strong interrater agreement for general competency [32]. Importantly, the CTRS includes a subscale assessing structural competency [31], in addition to scores for specific structural components and an overall competency score.

Given the volume of recorded sessions, CTRS scores will be generated for each session using the Lyssn platform. Lyssn [61] (pronounced “listen”) is a technology start-up that employs artificial intelligence (AI) to support training, supervision, and quality assurance of EBPs. Lyssn’s cloud-based platform provides the following: (1) user management and organization of sessions, clinicians, and supervisors; (2) recording, playback, and annotation of audio or video from therapy sessions; (3) speech-to-text transcription; (4) AI-generated fidelity and quality metrics; and (5) data summaries and visualizations for feedback. Session recordings are automatically transcribed using Lyssn’s speech recognition algorithms, which were trained on over 4000 sessions [62-64]. Using transformer-based deep neural networks [65], Lyssn developed AI-generated models for the 11 CTRS codes, trained on 2494 sessions with corresponding CTRS ratings within a cross-validation framework of training and test partitions [66,67]. Evaluation on a 30% test set of sessions, distinct from the training data, demonstrated strong predictive performance. For all but 1 code (*Understanding*, which is not a structural component of interest in this study), AI-generated predictions exceeded the 80% human reliability threshold. Using AI-generated metrics, the tools achieved 100% human-level reliability for total CTRS scores and demonstrated highly accurate reliability for individual items. Lyssn maintains an in-house coding team that continuously provides new validation and calibration data to monitor and sustain the performance of the AI algorithms.

While CTRS scores will serve as our primary fidelity metric, we will also examine self-reported fidelity to CBT structural components within the Tele-BE condition using web analytics data collected through the platform. As clinicians engage with Tele-BE, they will check off each structural component as it is completed in session or indicate if they intentionally override a component (Figure 1). This will provide self-reported data on structural component use for every recorded patient session in the Tele-BE condition. These data will allow comparison between self-reported use and Lyssn-generated CTRS scores, and provide insights into how and when clinicians override the Tele-BE infrastructure, informing aim 4 assessments of acceptability.

#### Quantitative Measures: Aim 3 Secondary Outcomes

Secondary outcomes are the target implementation mechanisms that align with our theorized mechanisms of action: intentions to use structural components of CBT and determinants of those intentions (Table 1). We will measure the strength of intentions separately for each structural component using established item stems from social psychology, designed to be adaptable to any behavior of interest [68]. Intentions will be assessed with 2 items on a 7-point scale, asking how willing and how likely a clinician is to use each component, with higher scores indicating stronger intentions. The 2 items will be averaged for each component. Determinants of intentions will be assessed through attitudes toward each component, measured with 4 standard semantic differential scales [40,69] (eg, 7-point scales ranging from “extremely unpleasant” to “extremely pleasant” or “extremely wise” to “extremely foolish”). Total scale scores will be computed by averaging all *z*-standardized items within each structural component, with higher scores indicating more favorable attitudes. *Norms* will be assessed using 2 standard item stems: the perception that “other people like me” will use the component, and that important others (eg, supervisors) will approve of their use, rated on a 7-point agreement scale. *Self-efficacy* will be measured with 3 statements on a 7-point scale assessing clinicians’ perceived ability to perform each component (eg, agreement with “If I really wanted to, I could use an agenda”). All items will be asked separately for each structural component and aggregated for the primary analysis, with exploratory analyses examining variation by component.

#### Quantitative Measures: Aim 4 Primary Outcomes

Primary outcomes for aim 4 include Tele-BE acceptability, feasibility, and any potential ethical concerns raised by clinicians or patients regarding the platform. Acceptability will be assessed using the AIM [52]. Feasibility will be examined through a combination of the FIM [52] and web analytics data. Tele-BE usability will be evaluated using the SUS [53]. Psychometric support for these measures has been described above under aim 1 activities. All measures will be administered to clinicians in both conditions to allow comparison of quantitative scores for acceptability and feasibility. These measures will be supplemented with clinician and patient interviews, which will also assess potential ethical concerns, including any pressure clinicians may have felt from the platform to deviate from care they believed was in the best interest of their patients.

#### Quantitative Measures: Aim 4 Secondary Outcomes

Aim 4 secondary outcomes include patient-level outcomes such as therapeutic alliance, symptoms and functioning, and treatment satisfaction. During the trial, therapeutic alliance will be assessed every 4 weeks from both the patient and clinician perspectives using parallel versions of the Working Alliance Inventory—Short Form (WAI-SF). The WAI-SF is a validated measure consisting of 12 items that ask respondents to rate their perceptions of the therapeutic relationship on a 5-point Likert scale [56]. Patient symptoms will be assessed using the Diagnostic and Statistical Manual of Mental Disorders Level 1 Cross-Cutting Symptom Adult Measure [58] (23 items rated on a 5-point scale from 0=none/not at all to 4=severe/nearly every day, covering 13 symptom domains), the 8-item Patient Health Questionnaire [57] (8 items rated on a 4-point scale from 0=not at all to 3=nearly every day, measuring depressive symptoms), and the 7-item Generalized Anxiety Disorder Scale [70] (7 items rated on a 4-point scale from 0=not at all to 3=nearly every day, measuring anxiety symptoms). These measures will be completed by patients at 4-week intervals. Patient functioning will be assessed using the WHO Disability Assessment Schedule 2.0 (WHODAS 2.0) [59], a 12-item measure rated from 1 (none) to 5 (extremely or cannot do) across 6 domains: cognition, mobility, self-care, getting along, life activities, and participation. WHODAS 2.0 will be administered at weeks 1 and 12. Questionnaires will be sent electronically to patients at the established intervals by research staff. Patient satisfaction, including any potential ethical concerns regarding their clinician’s use of Tele-BE, will be assessed qualitatively in a subsample of participants.

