**Methods:**

We will refine the Tele-BE prototype in collaboration with clinicians and supervisors, who are the target end users (aim 1). Working closely with our web development team, we will field test and iteratively refine Tele-BE using rapid-cycle prototyping to optimize user experience and fine-tune the BE strategies (aim 2). The revised platform will then be evaluated in a 12-week open trial involving 30 community mental health clinicians, who will be randomized to either Tele-BE or telehealth as usual. Each clinician will deliver treatment to 2 patients, resulting in a total of 60 patient participants. All sessions will be recorded and coded to assess CBT fidelity. Clinicians and patients will complete questionnaires at weeks 1, 5, 9, and 12, with qualitative interviews conducted at the end of the trial. Primary outcomes will focus on fidelity to CBT structural components, measured via coding of recorded sessions. Secondary outcomes will include target implementation mechanisms—intentions and their determinants (attitudes, norms, and self-efficacy)—assessed using mixed methods, as well as overall CBT fidelity (aim 3). Additionally, trial data will be used to evaluate the acceptability and feasibility of Tele-BE from both patient and clinician perspectives, along with any potential ethical concerns associated with its use (aim 4).

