#### Quantitative Measures: Additional Constructs

We will additionally assess 3 quantitative measures: (1) supervisory practices, (2) clinician social desirability, and (3) the cost of Tele-BE. Clinician-reported CBT-specific supervisory practices will be measured at weeks 1 and 12 to identify potential differences between conditions. We adapted the Self-Reported Therapist Intervention Fidelity for Youth Supervision, originally a supervisor-report measure of supervisory practices, to be inclusive of clinicians working with adult clients and to specifically capture supervision related to CBT structural components. The adapted supervisory measure consists of 14 items rated on a 7-point scale, indicating the extent to which specific supervisory techniques are used (1=not at all to 7=extensively). Additionally, the 17-item Edwards Social Desirability Scale will be included in the baseline clinician survey as a potential covariate for clinician-reported engagement with the Tele-BE platform [71]. Finally, we will track the following cost metrics to inform more formal cost evaluations in future studies: (1) anticipated annual cost per clinician user for Tele-BE, including variation based on the number of patients with whom the platform is used—these estimates will be calculated in collaboration with our web development team to account for both base subscription costs and ongoing web maintenance;; (2) time required to train clinicians to use Tele-BE, which we expect to be minimal, tracked for each clinician and averaged at study completion; and (3) time clinicians spend logged into the Tele-BE interface, captured via web analytics.

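### Patients are eligible from age 14, but the only version named for the broad symptom measure is the adult form, and nothing is said about ages 14 to 17

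*Protocol article*

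**What the plan says.** Under Participants and Procedures (aims 3 and 4), the protocol article sets the patient age criterion at "age 14 or older, consistent with the local age of consent for mental health services". The stated link to the local consent age shows that including minors is intended.

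Under Quantitative Measures: Aim 4 Secondary Outcomes, it says: "Patient symptoms will be assessed using the Diagnostic and Statistical Manual of Mental Disorders Level 1 Cross-Cutting Symptom Adult Measure". The only version named is thus the "Level 1 Cross-Cutting Symptom Adult Measure". It then describes a single fixed form: "23 items rated on a 5-point scale from 0=none/not at all to 4=severe/nearly every day, covering 13 symptom domains". The PHQ-8 and GAD-7 follow in the same list, and the section adds: "These measures will be completed by patients at 4-week intervals". Table 2 lists the instrument only as DSM level 1, without a version.

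The Abstract gives the planned number of patients ("resulting in a total of 60 patient participants"). No section says how many are expected to be under 18.

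**The concern.** The two statements do not fit together. Eligibility deliberately reaches down to 14, while the one version of the instrument that is named is, by its own title, for adults. The article is not silent on the version, which might have left the choice to a fuller protocol; it names the adult form and describes its items.

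What is at stake is how this outcome can be read. If patients aged 14 to 17 answer an adult-labelled form and are summarised together with adults, the combined score may mix responses that do not mean the same thing. The Overview of aims 3 and 4 says that a main purpose of the pilot is to test the feasibility of its design and measurement approach for a fully powered trial. A mismatch between the age criterion and an instrument is the kind of problem that would otherwise carry over into that trial.

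**Working it through.** No sample size, power or error rate is involved and the plan gives no figure to reproduce. The check sets the relevant statements of the protocol article side by side.

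1. **Who is eligible.** Age 14 or over, with no upper limit stated (Participants and Procedures).
2. **Which form.** One version, the adult one, with a fixed item count and number of domains (Aim 4 Secondary Outcomes). Table 2 adds nothing on version.
3. **Who completes it.** Patients, with no split by age (same section).
4. **Any provision for ages 14 to 17.** None is stated: no youth version, no age-dependent choice of form, no scoring rule for minors, no restriction to adults, no justification for the adult form in minors.
5. **Is age fit considered elsewhere?** Yes. Under Additional Constructs, a supervision measure of youth origin was adapted "to be inclusive of clinicians working with adult clients". That measure is reported by clinicians and concerns supervision, so it is context only and does not show that a patient scale was overlooked.
6. **Do the planned analyses settle it?** Quantitative Analyses enters patient demographics, including age, as covariates. A covariate can remove an average difference in score by age. It does not test whether a given score reflects the same symptom severity, or responds to change in the same way, at 14 as in an adult. Preliminary Analyses plans psychometric checks such as coefficient alpha. An alpha computed over all patients measures internal consistency in the mixed sample, not comparability between age groups.
7. **Size.** The number of minors, m, is not given, so 0 ≤ m ≤ 60 and the affected share is m/60, from 0% to 100%. How far an adult form would misstate symptoms at 14 to 17 is also not given. No numerical effect follows from the document.
8. **Reach.** This is one of three symptom scales (DSM level 1, PHQ-8, GAD-7), listed with the WHODAS 2.0 under one aim 4 secondary outcome. The aim 3 primary outcome is coded session fidelity. The Progression Criteria use AIM and FIM scores, CTRS fidelity trends and qualitative findings on motivation. None of these uses the symptom scales.

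**The case against.** The strongest reply is that no sentence says minors receive the adult form. One might point to the statement that participants "complete the same assessment battery, except that participants in the Tele-BE condition will also respond to condition-specific qualitative interview questions", but it concerns equality between the two conditions and says nothing about age. That is right, and the point does not rest on it. An age-dependent form could also sit in a full protocol that is not shown. This carries less weight, because the article commits to one named version and describes its items.

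It can also be said that harm is not shown. Whether the adult form performs differently at 14 to 17 is a psychometric question that the article does not address. This stands: the document supports a mismatch of label and eligibility, not a demonstrated error in scores. Repeated measurement lets each patient be compared with their own baseline on the same form. That softens differences in level, but does not establish equal sensitivity to change.

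Two stronger readings are tempting and should be resisted:

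- **Bias between arms.** A reader might infer that adolescent caseloads concentrated in one arm would bias the comparison. The article gives no information on caseload age. It balances allocation within organizations, which limits imbalance to the extent that caseload age differs by agency, and it adjusts for age. The inference is unsupported.
- **PHQ-8 and GAD-7 as the answer for all ages.** A reader might infer that these two scales suit every patient because the article attaches no adult label to them. A missing label is not evidence of suitability, and the article gives no age range for either.

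**Conclusion.** The point holds as a stated mismatch: patients from age 14 are eligible, the adult version is the only one named for this measure, and nothing is provided for ages 14 to 17. That minors would complete the adult form and be summarised with adults is the plain consequence of the text as written, since no exception or separate summary by age is described; it is not an explicit statement.

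The size is unknown and cannot be bounded more tightly than 0 to 60 patients. The point has no practical effect if no minors enrol. Even if many do, it reaches one aim 4 secondary measure that the article presents as exploratory. The primary outcome and the decision to progress are untouched. This is a worthwhile, low-cost improvement, not a threat to the trial's main conclusions.

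**What to change.** In Quantitative Measures: Aim 4 Secondary Outcomes, and in the matching row of Table 2, adopt one of two options:

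- restrict both administration and summary of the DSM Level 1 measure to patients aged 18 or over; or
- give patients aged 14 to 17 a version made for their age, name it, and summarise it separately from the adult scores.

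Either option needs an age branch in the electronic questionnaire and leaves fewer patients in the analysis of this measure. Under the second, the group of minors may be too small for more than description. The Results section reports only aim 1 recruitment as under way, so on the article's own timeline the change can be made before aim 3 data collection begins.
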